## Abstract

**Introduction:**

Pulmonary embolism (PE) is a potentially fatal condition requiring timely diagnosis and treatment. CT pulmonary angiography (CTPA) is the gold standard for diagnosis and indicates PE severity through radiological markers of right heart strain. However, accurate interpretation and communication of these findings is often suboptimal in real-world practice. Artificial intelligence (AI) could alleviate pressure on radiology services by supporting PE identification, risk stratification and worklist prioritisation. Before widespread adoption, AI tools must be rigorously validated for diagnostic accuracy, safety and clinical impact.

**Methods and analysis:**

This pragmatic single-centre, non-randomised quasi-experimental study will evaluate the diagnostic accuracy, feasibility, and clinical-cost impact of AI-assisted PE detection and risk stratification using AIDOC and IMBIO software. We will recruit two consecutive cohorts of adult patients undergoing CTPAs for suspected PE: a comparator cohort (12 months pre-AI implementation) and an intervention cohort (12 months post-AI implementation). AI will be applied retrospectively to the comparator cohort, while in the intervention cohort, radiologists will have contemporaneous access to the AI’s interpretation of CTPA images.

A subset of retrospective scans, both PE-positive and PE-negative, will undergo expert thoracic radiologist review to establish a reference standard. Data on patient demographics, clinical management and outcomes will be collected. Clinical management pathways and patient outcomes will be compared between cohorts to assess AI’s influence on acute PE management. Health economic modelling will assess the cost-effectiveness of integrating AI technology within the diagnostic workflow of acute PE.

**Ethics and dissemination:**

This study was approved by the UK Healthcare Research authority (IRAS 311735, 10 May 2023). Ethical approval was granted by West of Scotland Research Ethics Service (23/WS/0067, 3 May 2023). Results will be shared with stakeholders, presented at national and international conferences, and published in open-access peer-reviewed journals.

**Trial registration number:**

NCT06093217.

STRENGTHS AND LIMITATIONS OF THIS STUDYThis quasi-experimental study will use retrospective and prospective cohorts to evaluate the real-world clinical and economic impact on patients with suspected acute pulmonary embolus (PE) of integrating artificial intelligence (AI) for detection and risk stratification of PE into radiology workflows.The clinical ground truth will be re-established in a retrospective cohort via expert thoracic radiologist review.Comprehensive data collection, capturing a range of clinical and radiological endpoints, will enable robust, multidimensional analyses of the clinical and economic impact of implementing AI.As a single-centre study, findings may support future national, multi-centre research validating AI for acute pulmonary embolism detection and risk stratification in broader populations.

## Introduction

### Background

 Pulmonary embolism (PE) is a potentially fatal condition that may cause right ventricular failure and death if not recognised and treated promptly. In the UK, PE accounts for almost 70 000 hospital presentations and 37 000 hospital admissions per year.^1^ This places a substantial financial and operational burden on the NHS. Although it is difficult to know precise cost estimates, the total cost burden for venous thromboembolism is estimated at £640 million per year.^2^ Furthermore, the incidence of PE is rising.^3^,^5^ This trend can be partially explained by the increasing availability and improved quality of diagnostic imaging. However, demographic and clinical factors, such as increased survival among patients with major prothrombotic comorbidities and obesity, are also likely to contribute to this increase.^6^

Although falling, mortality from PE remains significant. It accounts for up to 6.5 deaths per 100 000 population per year.^6^ The reduction in mortality is attributed to improved interventions, including direct oral anticoagulants, better management guidelines^7^ and increased diagnosis of smaller, subsegmental emboli.^8^ However, despite advances in PE detection and clear national guidance on acute PE treatment, risk stratification and management are still performed poorly.^9^

Radiological imaging plays a critical role in the PE pathway. Multi-detector CT pulmonary angiography (CTPA) is considered the gold standard imaging modality for PE diagnosis. CTPA can also provide important, prognostically relevant information on right heart strain (RHS).^10 11^ This includes reversal of the right ventricular to left ventricular ratio (RV:LV), interventricular septal straightening and contrast reflux in the inferior vena cava. These indirect markers can inform risk stratification and subsequent clinical medical management.

The NHS Long Term Plan outlines the importance of innovative, affordable technologies to improve diagnosis, risk assessment and treatment of respiratory conditions, including PE.^12^ Achieving this depends on accurate image interpretation and timely communication of findings. However, national audits, including the National Confidential Enquiry into Patient Outcome and Death, have highlighted deficiencies in PE reporting and downstream clinical.^9^

### Challenges in current practice

While CTPA is widely available and has high diagnostic accuracy for detecting acute PE, growing demand places increasing pressure on radiology departments.^13^ These pressures, particularly during times of service strain, can contribute to delays in scan interpretation and increase the likelihood of fatigue-related diagnostic errors.^14^ Additionally, interobserver variability remains a persistent challenge. Non-specialist radiologists may differ in their ability to confidently identify prognostically significant features of radiological RHS despite their clinical relevance. Consequently, radiological reporting of the RV:LV ratio is often inconsistent or omitted altogether.^9 15^ This variability undermines the standardisation of acute PE care and may lead to missed opportunities for both escalation of treatment in high-risk patients and timely discharge in those identified as low risk.

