### Participant data

Clinical, radiological and patient-related outcomes will be extracted for each participant using a combination of electronic and paper-based systems. Primary data sources will include electronic health records, integrated care records, RIS and physical patient notes where relevant. Data extraction will be conducted by trained members of the research team using a pre-specified case report form (CRF) to ensure consistency.

The following data types will be collected for each participant:

Demographics: age and sex.Anthropometrics: height, weight and body mass index.Referral context: date and time, outpatient or inpatient location.Admission/discharge details: admission and discharge date and time.Comorbidities: structured past medical history entries and coded diagnoses.Physiological parameters: vital signs closest to the time of CTPA request (ie, heart rate, blood pressure, oxygen saturation, respiratory rate).Biochemistry markers: including, but not limited to, d-dimer, troponin, brain natriuretic peptide.Imaging history: chest radiography, echocardiography, lower extremity limb Doppler ultrasound.Medication history: including, but not limited to, anticoagulants, antiplatelets and time to anticoagulation initiation.Patient management details: time of first clinical review, location of ongoing care and referrals to respiratory, thrombosis and haematology clinics.Acute PE severity assessment: simplified pulmonary embolism severity index (sPESI) and the Geneva Score calculated based on recorded clinical parameters.^20 21^Clinical outcomes up to 12 months after their CT data: including, but not limited to, intensive care admission, haemodynamic instability, thrombolysis administration, re-presentation to the emergency department, re-admission to the hospital, major and minor bleeding events and all-cause mortality.

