### Statistical analysis

#### Clinical and radiological outcomes

Our primary outcome will be the proportion of patient decisions made in line with evidence-based best practice guidelines after introducing AI technology within CTPA reporting. Secondary outcomes relate to acute PE detection, RV:LV ratio quantification and clinical and operational endpoints including mortality, length of stay, readmission, follow-up and cost to NHS (table 1).

**Table 1 T1:** Primary, secondary and additional outcomes

Outcome measure	Measure description
Primary outcome measure	
Proportion of patient decisions made in line with evidence-based best practice guidelines after introducing AI technology within CTPA reporting	Comparison before and after AI introduction
Secondary outcome measures	
Rate of acute PE detection with AI technology	True positives and true negatives
Rate of discordant acute PE cases	False positive and false negative rate with acute PE detection
AI failure rate for acute PE detection	Proportion of scans unable to be interpreted by AI despite suitable CTPA acquisition
Rate of RV:LV detection with AI technology	True positive and true negative
Rate of discordant RV:LV detection	False positive and false negative
Failure rate for automated RV:LV ratio	Proportion of scans unable to calculate automated RV:LV ratio despite suitable CTPA acquisition
30-day mortality	Patient mortality (death) at 30-days post-PE diagnosis. Comparison before and after AI introduction
12-month mortality	Patient mortality (death) at 12 months post-PE diagnosis. Comparison before and after AI introduction
Hospital admission and bed days for acute PE	Comparison before and after AI introduction
Time to anticoagulation in PE cases	Comparison before and after AI introduction
Time from CTPA to discharge	Comparison before and after AI introduction
PE risk stratification rates (low, intermediate low, intermediate high and high risk)	Comparison before and after AI introduction
Cost to NHS for acute PE	Comparison before and after AI introduction
End-user (clinician and radiologist) acceptability of AI technology	Quantified metrics from a non-validated questionnaire to evaluate end-use experience of integrated AI radiology reporting
Referral rates to outpatient follow-up (respiratory, thrombosis, haematology)	Comparison before and after AI introduction
Diagnostic rate of chronic thromboembolic pulmonary hypertension	Comparison before and after AI introduction
Additional outcome measures	

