Exploratory outcomes	Given the exploratory nature of this observational non-randomised feasibility study, there may be patterns/outcomes which emerge/develop during the study period. The investigators will report on any patterns that may emerge following the introduction of AI reporting

AI, artificial intelligence; CTPA, CT pulmonary angiography; PE, pulmonary embolism; RV:LV, right ventricular to left ventricular ratio.

Descriptive statistics will summarise participant baseline characteristics and comorbidities, separately in the comparator and intervention cohorts. Our primary analyses will consist of comparisons between the comparator and intervention cohorts, with continuous outcomes analysed using t-tests and categorical outcomes using χ^2^ tests. To account for and disentangle any possible underlying time trends from the effects of AI introduction, regression models will be used to compare outcomes. These will include covariates that allow for a linear trend in the pre-implementation phase, a step change at the point of AI implementation, and a modification to the linear trend following this.

Kaplan-Meier survival curves will quantify differences between time-to-event outcomes in the two cohorts. Cox regression models will also be used to summarise the difference between cohorts. If feasible, regression models will be adjusted for known predictors of outcome from both Geneva and sPESI scoring systems.^20 21^ Missing values will be handled by performing each analysis excluding patients who have relevant data missing for the variables concerned. Statistical significance will be set according to p value <0.05.

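### Referral time is recorded for every participant, but neither the unadjusted primary comparison nor the named regression covariates use hour or weekday of referral, so a change in out-of-hours mix between the two years could enter the AI estimate

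*Protocol article*

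**What the plan says.** Four places in the protocol article bear on this.

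- **Challenges in current practice** links demand on radiology to reading performance: "These pressures, particularly during times of service strain, can contribute to delays in scan interpretation and increase the likelihood of fatigue-related diagnostic errors". It does not define strain and does not mention nights or weekends.
- **Participant data** lists, for each participant, "Referral context: date and time, outpatient or inpatient location".
- **Clinical and radiological outcomes** sets the primary outcome: "Our primary outcome will be the proportion of patient decisions made in line with evidence-based best practice guidelines". The primary analyses compare the two cohorts directly, "with continuous outcomes analysed using t-tests and categorical outcomes using χ^2^ tests".
- **The same section** then adds models for calendar time: "To account for and disentangle any possible underlying time trends from the effects of AI introduction, regression models will be used to compare outcomes". Their terms are described so: "These will include covariates that allow for a linear trend in the pre-implementation phase, a step change at the point of AI implementation", followed by a change in slope afterwards. Patient-level adjustment is conditional: "If feasible, regression models will be adjusted for known predictors of outcome from both Geneva and sPESI scoring systems".

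No hour-of-day, weekday or workload term is named in any of these analyses.

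**The concern.** This is a non-randomised comparison of one year with the next at one hospital. Any determinant of outcome whose distribution changes between the years is a possible confounder. Several outcomes in Table 1 are process measures that could plausibly depend on when a patient is referred: time to anticoagulation, time from CTPA to discharge, and bed days. The primary outcome is exposed less directly, through what the report says and what clinicians then decide.

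Geneva and sPESI predictors describe the patient, so they do not stand in for the hour of referral. Referral precedes the scan, so the AI cannot change that patient's referral time, and it is a legitimate baseline covariate. The section on clinical management expects outcome differences to reflect use of the AI findings rather than specialist services. It does not consider service conditions at referral as another explanation.

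At stake are a small bias in the AI estimate and some unexplained variance that could be removed with data already in hand.

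**Working it through.** The article states no power, effect size or bias figure, so there is nothing to reproduce. What follows is illustration. Mix shifts, outcome gaps and baseline proportions are assumptions.

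**Numbers of patients.** From the sample size section: about 3500 CTPAs and a PE prevalence of 12% to 15%. This gives 3500 × 0.12 = 420 to 3500 × 0.15 = 525 PE cases, or 210 to about 263 per cohort with an equal split (assumed). PE-positive patients are taken as the analysis set. If the primary outcome used a larger denominator, the standard error would be smaller and a given bias would weigh more.

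**Formulas.** Bias in the crude difference = change in out-of-hours share × outcome gap between out-of-hours and in-hours. False-positive rate = P(|Z + bias/SE| > 1.96), two-sided 5% assumed.

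**Primary proportion.** Assume 60% concordance, a gap of 10 to 20 points and a mix shift of 5 to 10 points.
- Bias: 0.05 × 10 = 0.5 to 0.10 × 20 = 2.0 points.
- SE: √(2 × 0.6 × 0.4/210) = 4.8 points; √(2 × 0.6 × 0.4/263) = 4.3 points.
- False-positive rate: 0.5/4.8 = 0.10 gives 5.1%; 2.0/4.3 = 0.47 gives 7.5%.
- For scale, the difference detectable with 80% power from 60% is 12.9 points (n = 210) or 11.6 points (n = 263).

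Wider assumptions (70% concordance, gap 5 to 20 points, shift 2 to 15 points) give a bias of 0.1 to 3.0 points, an SE of 4.0 to 4.5 points and a rate of 5.0% to 11.7%. The largest bias is 0.75 SE.

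**Timed outcomes.** Assume a gap of 0.3 to 0.7 SD and a shift of 5 to 10 points.
- Bias: 0.3 × 0.05 = 0.015 SD to 0.7 × 0.10 = 0.07 SD.
- SE: √(2/210) = 0.098 SD; √(2/263) = 0.087 SD.
- False-positive rate: 0.015/0.098 = 0.15 gives 5.3%; 0.07/0.087 = 0.80 gives 12.6%.
- If half of referrals are out of hours, timing explains 0.25d²/(1 + 0.25d²) of the variance: 2.2% at d = 0.3 and 10.9% at d = 0.7.

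All these rates use the crude two-sample SE, so they describe the unadjusted tests.

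**The planned segmented model.** Trend, step and slope change were fitted to noise-free monthly means (12 months, 1-month gap, 12 months), with outcomes 20 points worse out of hours:

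| Change in mix | Crude difference | Step | Slope change per month |
|---|---|---|---|
| Linear drift, 10 points between cohort means | −2.0 points | 0 | 0 |
| Abrupt 10 points at go-live | −2.0 points | −2.0 points | 0 |
| Abrupt 10 points, six months into the post phase | −1.0 point | +0.4 points | −0.25 points |

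**Precision of the step.** With patients spread evenly over each year and separate slopes, the variance of a fitted line at the end of its 12 months is (1 + 3)σ²/n. Extrapolating one line across the 1-month gap makes it (1 + 7²/12)σ²/n = 5.08σ²/n. The step variance is then 9.08σ²/n, against 2σ²/n for the crude difference, so its SE is √(9.08/2) = 2.1 times as large. Taking the ratio as 2, the worst cases above fall from 12.6% to about 6.9% (timed outcome) and from 7.5% to about 5.6% (primary proportion).

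**The case against.** The strongest reply is that nothing here is stated wrongly. The introduction says only that pressures can contribute to delay and error, and it ties them to growing demand, which is a calendar trend. The regressions model calendar time explicitly, and a linear drift in mix leaves their step term unbiased. Both cohorts are consecutive scans from one centre over 12 months each under the same eligibility rules, and nothing suggests that referral hours changed. The covariates described need not be exhaustive, and a condensed article may leave the full list to documents not shown. Referral time is also not reading time: a scan requested in hours may be read out of hours.

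Much of this stands. A reader might infer that no planned model uses the recorded date, or that a change in out-of-hours mix is bound to be counted as an AI effect. The documents support neither. Calendar time underlies the trend terms, and only hour and weekday go unused. Confounding needs both a real mix change and an outcome gap, and no figure is given for either. Treating out-of-hours as a marker of strain is an inference, not the protocol's definition.

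The reply does not dispose of the point. The article itself makes the unadjusted tests primary, and even a linear drift passes into those in full. The trend terms also do not protect against an abrupt shift at or after go-live.

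**Conclusion.** The point holds in a limited form. Hour and weekday of referral are available before the scan for every participant, yet they are absent from the primary comparison and from the named covariates. A difference in referral mix between the years could therefore enter the crude estimate and, if abrupt at or after go-live, the step or slope-change terms.

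The likely size is modest. On the primary proportion the assumed bias is under half a standard error. The timed outcomes are more exposed, but the 12.6% figure needs every assumption at its extreme and applies only to the unadjusted test. Whether any bias arises depends on a mix change and an outcome gap that the documents do not give. This is an inexpensive improvement to the analysis, not evidence that the planned result would be misleading.

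**What to change.** In the regressions for the primary outcome and the timed outcomes, add two indicators derived from the recorded referral timestamp: in-hours versus out-of-hours, and weekday versus weekend or bank holiday. Define both before outcomes are compared between cohorts. Keep them whether or not the Geneva and sPESI adjustment proves feasible.

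Base the conclusion about the AI effect on this adjusted model and present the t-test and χ² results as descriptive. Adding covariates to the regressions alone would leave the primary tests as exposed as before.

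The covariates need no new data and use two degrees of freedom; for outcomes with few events, such as 30-day deaths, use the out-of-hours indicator alone. Resting the conclusion on the segmented model has a price in precision, since the step's standard error is about twice the crude one, and the report should say so. It should also say that referral time is an imperfect proxy for strain when the scan is read. A breakdown of the AI effect by in-hours and out-of-hours is optional and should be labelled exploratory, because it divides 210 to 263 PE patients per cohort further.

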### Artificial intelligence in radiology

Artificial intelligence (AI) assisted image interpretation of CTPA scans offers a potential solution to these challenges. AI algorithms may enhance reporting accuracy, reduce inter-reporter variability, prioritise high-risk cases and support workflow efficiency for acute PE. AI tools have demonstrated strong performance compared with acute reporting radiologists in acute PE identification with reported sensitivities and specificities as high as 97% and 100% respectively.^16 17^ AI algorithms have also been shown to outperform radiologists in the detection of PE and improve reporting times through case prioritisation.^16 18^

Although AI algorithms for RHS are less well established, early studies suggest they can reliably quantify RV:LV ratio.^10^ Further validation of these algorithms in prospective populations and within the UK is required. Furthermore, few studies have evaluated the clinical utility or cost-effectiveness of integrating such AI software into radiology workflows in real-world settings.

### Study aims and objectives

This study aims to evaluate the real-world clinical and financial impact of integrating AI algorithms into radiological workflows for the assessment and management of acute PE within a single-centre, district general hospital. The study will evaluate the implementation of two commercially available, Food and Drug Administration (FDA) approved AI tools designed to assist radiologists with acute PE detection and quantification of RHS.

The study will examine whether AI integration can improve accuracy of PE diagnosis, enhance risk stratification through RHS quantification, and support downstream clinical decision-making. The study will compare the outcomes observed between a pre-AI and post-AI implementation cohort.

The research team hypothesises that AI-assisted interpretation of CTPA will lead to earlier identification of high-risk patients, minimise delays in critical decision-making and contribute to more consistent application of evidence-based PE management strategies.

## Methods: participants, interventions and outcomes

This study protocol was designed in accordance with Standard Protocol Items: Recommendations for Interventional Trials guidelines.^19^

